## Abstract

**Introduction:**

Functional seizures (FS) are events that resemble epileptic seizures, but are not attributed to brain pathology and are instead thought to be due to psychological factors. A small, multisite, open-label, single-arm, pilot trial of a breathing intervention known as breathing control training (BCT) found it to be safe and effective in reducing seizure frequency in FS. We propose a protocol for a study to confirm these results.

**Methods and analysis:**

A 24-week, multicentre, individually-randomised, assessor-blinded, two-arm, parallel-group efficacy and acceptability trial of BCT versus control (Befriending) in 220 participants ≥16 years of age with FS. Eligible participants will be randomly allocated to receive two sessions of either BCT or Befriending over a 4-week period. Sessions will be delivered by a respiratory physiotherapist at a clinical care site or via telehealth. They will complete assessments prior to commencing treatment and at 4, 12 and 24 weeks after their initial session of BCT/Befriending. The trial will be conducted alongside treatment as usual. An economic evaluation including cost-utility and cost-effectiveness analyses will be carried out from health sector and societal perspectives.

**Ethics and dissemination:**

The study has been approved by The Austin Health Human Research Ethics Committee (HREC/84335/Austin-2022) and the New Zealand Central Health and Disability Ethics Committee (2022 FULL 12324). Findings will be reported to trial participants and consumers; presented at local, national and international conferences; and disseminated by a peer-reviewed scientific journal.

STRENGTHS AND LIMITATIONS OF THIS STUDYThe study has a large sample, and an international, multicentre design.The study uses a control arm matching the intervention for therapist time, and delivered by the same therapist.The study is only blinded to assessor; participant and therapist blinding is not possible.

## Introduction

### Background and rationale

 Functional seizures (FS; also known as psychogenic or non-epileptic seizures) are events that resemble epileptic seizures, but are not attributed to brain pathology and are instead thought to be due to psychological factors.^1^ FS can occur many times per day, and their impact on patients and families is often disastrous, with most patients unable to work or study.^2^ FS affect all ages, with median onset in the 30s, and women three times more likely to be affected than men.^3^ People with FS are heavy users of a range of healthcare resources and are usually economically dependent.^4 5^ Studies show mortality is as increased in patients with FS as it is in those with epilepsy,^6^ and quality of life is significantly worse.^7^ It is common in neurological and epileptological practice, with an incidence of 7 per 100 000 per year, and a prevalence of approximately 0.05% of the general population.^8 9^ Despite this, treatment options for FS are limited.

The recommended treatment for FS is usually psychotherapy; however, a review of psychotherapy found no validated treatments offering sustained benefit.^10^ Psychological interventions are also resource demanding and expensive, and in many countries, limited by the availability of specialised psychologists and funding for them. Further, patient compliance is problematic and many patients do not attend or complete therapy,^11^ in large part because of the stigmatisation of psychiatric diagnoses.^12^ There is a need to develop a simpler and more acceptable treatment for patients with FS.

There is an association between FS and panic attacks, though the reason for this is unclear.^13^ We propose that the association is due to a common mechanism—hyperventilation. Symptoms of hyperventilation are commonly associated with FS,^13^ and FS can often be induced by asking patients to hyperventilate,^14^ suggesting a role for hyperventilation in the initiation of FS. We have confirmed this in our observations of 107 video electroencephalography (video EEG) recordings of patients with FS, finding a significant rise in respiratory rate in the minutes before the onset of seizures in most people.^15^

In patients with asthma, a therapy known as breathing control training (BCT) improves hyperventilation symptoms as shown on the Nijmegen scale of hyperventilation, anxiety and depression scores, and quality of life, but does not affect measures of airway function.^16^ We hypothesise that the same therapy when used for FS will improve breathing control, reduce hyperventilation and thus reduce the frequency of episodes. A standard course of BCT takes a single 1-hour session and a half-hour ‘refresher’ session at 1 month, administered by a physiotherapist. Its resource cost is substantially less than psychological interventions, which require several sessions, often more, by a specialised clinical psychologist. Even if BCT is effective in only a subset of patients, then it is likely to be very cost-effective, especially if we are able to determine which subset is likely to respond. BCT has the further advantage that it is likely to be acceptable to patients who may be deterred by psychological interventions, as it does not require that the patient frame or reframe their disorder as psychiatric.

We conducted a multisite, open-label, single-arm, pilot trial of BCT in FS.^17^ Participants with FS over the age of 16 years received an hour of breathing training from a respiratory physiotherapist, with a half-hour booster session a month later. Seizure frequency and Nijmegen scores (a measure of hyperventilation) were reported at baseline and follow-up, 3–4 months later. 18 subjects were recruited, and 10 completed follow-up. 7 of these 10 had improved seizure frequency, of which 3 achieved seizure remission, and 3 did not, with seizure frequency correlating with Nijmegen score (Spearman’s rank correlation=0.75). The intervention was well tolerated, with no adverse events (AEs) reported.

This provides preliminary data that BCT may be safe and effective for this patient group. This protocol is for a multicentre, randomised controlled trial to confirm these results.

### Study objectives

To establish the efficacy, acceptability and cost-effectiveness of BCT compared with Befriending in people ≥16 years of age with FS in a 24-week, multicentre, assessor-blinded, individually-randomised controlled superiority trial. In addition, for participants with routinely monitored transcutaneous carbon dioxide (tcCO_2_) during video EEG, we will examine if a respiratory biomarker of hyperventilation, tcCO_2_, will predict treatment response to BCT.

### Study hypothesis

We hypothesise that the proportion of patients with seizure remission, defined as FS frequency of zero in the preceding 4 weeks (recorded by the participant in a seizure frequency diary) at 12 weeks after initial treatment will be higher in the group of patients randomised to BCT compared with those randomised to control (Befriending).

Further, BCT will be as acceptable to patients and cost-effective compared with standard care for FS. In addition, we hypothesise that quality of life, work and social functioning, depression and anxiety symptoms, and hyperventilation tendency will improve more with BCT than control.

As an exploratory hypothesis, we expect hyperventilation preceding or during seizures will predict response to BCT, and that hyperventilation measured by expired carbon dioxide (CO_2_) will be clinically identifiable (by association with convulsive seizure phenomenology, childhood trauma history and increasing pre-ictal heart rate).

## Methods and analysis

### Trial design

A 24-week, multicentre, individually-randomised, assessor-blinded, two-arm, parallel-group efficacy and acceptability trial of BCT versus control (Befriending) in 220 participants ≥16 years of age with FS. Eligible participants will be randomly allocated (1:1) to receive two sessions of either BCT or Befriending with a respiratory physiotherapist over a 4-week period. They will complete assessments at baseline (prior to commencing treatment) and 4 weeks, 12 weeks and 24 weeks post their initial session of BCT/Befriending. The trial will be conducted alongside their standard care (treatment as usual). Optional, longitudinal observational follow-up will be conducted 52 weeks, 78 weeks and 104 weeks after their initial treatment session.

### Study setting

The trial will be conducted at four public hospitals in Melbourne, Australia (Austin Health, The Alfred, Royal Melbourne Hospital (RMH) and St Vincent’s Hospital Melbourne (SVHM)) as well as the New Zealand Brain Research Institute (NZ BRI) in Christchurch, New Zealand. Telehealth appointments will be used when in-person appointments are not feasible.

### Patient and public involvement

Patients were involved in the design and conduct of the trial. A representative of the consumer organisation for functional neurological disorders (FND), ‘FND Hope’, contributed to the design of the study and to obtaining funding, and sits on the trial steering committee.

### Intervention and comparator

#### Breathing control training

BCT includes teaching appropriate rate and depth of breathing and the development of a pattern of breathing appropriate to current physical activity. The elimination of dysfunctional breathing patterns, including hyperinflation and hyperventilation, is discussed. Diaphragmatic breathing is taught, and emphasis is placed on calm, slow, nasal expiration. Education on stress responses and their interactions with breathing patterns is given. The integration of appropriate breathing and relaxation techniques into daily living activities is encouraged. Initially, exercises are taught in a semi-recumbent position, progressing to sitting, then standing, then during everyday activities. Finally, the integration of breathing and relaxation techniques into speech is taught and practiced. Home exercises are given, with daily practice encouraged (5–10 min, two times a day) and recorded in a diary provided to participants.

The BCT will be delivered by a respiratory physiotherapist with specific training in this technique. They will conduct a 60-minute initial session with the participant (one-on-one) and a 30-minute refresher session 4 weeks later. The physiotherapist will administer the Brompton Breathing Pattern Assessment Tool (BPAT) in both sessions to assess for and monitor levels of breathing pattern irregularities.

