#### Befriending (control)

The control condition, Befriending, is specifically designed to be the control intervention for clinical trials of psychology-based or ‘talking’ therapies. It offers the same clinician contact and involves meeting and talking with the participant in a supportive, friendly, but non-directive manner. It has been manualised and its outcomes formally assessed to allow it to serve as a theoretically justified ‘placebo’ group. It has become the standard control group in therapy trials for mental health, as it matches for expectancy, acceptability, enjoyment and engagement, while delivering no specific benefit on most outcomes.^18^ It will be administered by the same clinicians (physiotherapists) at intervals and duration matching the BCT sessions.

To provide equal opportunities, participants in the Befriending (control) group will be offered access to the BCT intervention (initial and booster session) after they have completed their 24-week follow-up questionnaires.

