### Outcomes

Primary, secondary and exploratory outcomes are outlined in table 2, box 1.

**Table 2 T2:** Procedures in the trial that are in addition to standard care (alongside ‘treatment as usual’)

Procedure	Time/visit	Dosage/volume
BCT/Befriending sessions	Baseline and 4 weeks later	60 min initial session; 30 min second session
Seizure frequency diary	Completed by the participant as seizures occur throughout the 24-week study period	~1 min per week
Breathing exercises (BCT participants only) and adherence diary	Following the baseline session, through to Week 12	5–10 mins, two times a day
Self-report questionnaires	Baseline, Week 4, Week 12 and Week 24	30–45 mins
LEDS (optional)	Week 12	LEDS (optional) Week 12 ~2 hours

BCT, breathing control training; LEDS, Life Events and Difficulties Schedule.

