Box 1OutcomesPrimarySeizure remission, defined as seizure frequency of zero in the preceding 4 weeks (recorded by the participant in a seizure frequency diary), measured at Week 12 (12 weeks post the initial treatment session).SecondaryChanges in hyperventilation from baseline, measured by the Nijmegen scale of hyperventilation provided at baseline, Week 4, Week 12 and Week 24.Changes in healthcare utilisation from baseline, measured via a tailored resource use questionnaire provided at baseline, Week 12 and Week 24, as well as changes in health service use ascertained from Services Australia and CVDL data (Services Australia and CVDL data for consenting participants only).Changes in quality of life from baseline, measured by the Assessment of Quality of Life Eight Dimension provided at baseline, Week 4, Week 12 and Week 24.Changes in depression and anxiety symptoms from baseline, measured by the 9-item Patient Health Questionnaire and Generalised Anxiety Disorder Assessment respectively, provided at baseline, Week 4, Week 12 and Week 24.Changes in occupational and social functioning from baseline, measured by the Work and Social Adjustment Scale provided at baseline, Week 4, Week 12 and Week 24.Acceptability of BCT captured by a tailored self-report questionnaire provided after attending the Week 4 ‘booster’ session.Safety of BCT assessed by the occurrence of adverse events reviewed at Week 4, Week 12 and Week 24.tcCO_2_ levels (mm Hg; a marker of hyperventilation) preceding or during seizures, BPAT score (at baseline) and/or Nijmegen score (at baseline), to predict response to treatment.ExploratoryThe presence of significant life events in childhood and adolescence (≤16 years of age), and 12 months preceding the onset of their FS, assessed via the Childhood Experience of Care and Abuse Questionnaire and the LEDS*, respectively, to gauge moderators of treatment response.The MDI and Toronto Alexithymia Scale provided at baseline will be assessed if predictors of treatment response. MDI scores at Week 4, Week 12 and Week 24 will be assessed if they correlate with treatment response.*Note, the LEDS is optional, and only relevant to participants whose FS have started within the last 2 years.BCT, breathing control training; BPAT, Brompton Breathing Pattern Assessment Tool; CVDL, Centre for Victorian Data Linkage; FS, functional seizures; LEDS, Life Events and Difficulties Schedule; MDI, Multiscale Dissociation Inventory; tcCO_2_, transcutaneous carbon dioxide.

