##### Brompton Breathing Pattern Assessment Tool

A 7-item, respiratory clinician-administered instrument which can be used to assist in identifying dysfunctional breathing patterns. It requires the clinician to count the patient’s respiratory rate and observe their breathing pattern for 1 min before rating each item 0–2. Items include a rating of abdominal or upper chest movement, inspiratory flow, expiratory flow, channel of inspiration and expiration, air hunger, respiratory rate and rhythm. A total BPAT score ≥4 is indicative of breathing pattern disorders with a sensitivity of 92% and specificity of 75%.^28^

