## Discussion

This study described the design and methodology of the first multicentre, randomised, assessor-blinded, two-arm, parallel-group efficacy and acceptability trial of BCT versus control in patients with FS. Despite increased research in interventions for FS, and an abundance of smaller studies suggestive of therapeutic effect, there remain no definitive, validated treatments.^10^ Once completed, this study will represent only the second appropriately powered, multicentre, randomised trial of an intervention for FS.^22^ We hypothesise that BCT will reduce the seizures and related symptoms of FS greater than a control intervention designed to provide no benefit.

BCT has been found to be safe and well-tolerated when provided to people with respiratory conditions.^25^ As a brief intervention, it should prove cheap to deliver, and as an allied health intervention, it may prove more acceptable than psychotherapy interventions, where large proportions will not participate or complete the intervention.^22^ Its efficacy in FS remains to be determined, as it has not been subject to a trial other than our own pilot.^17^

The mechanism of any effect remains to be determined, but the therapy was designed to address abnormal breathing patterns, particularly hyperventilation, and in our pilot study, improvement correlated with improvement in this. People with FS do commonly have abnormal breathing, not only around the time of their FS.^13^ There are a priori reasons to think the intervention may work in FS, in the same way that it has worked in asthma. A goal of this study is to explore the mechanism of any effect, particularly in regard to breathing pattern, whether measured by clinical observation of breathing patterns, questionnaires or CO_2_ measurements. If the intervention is only effective in a subgroup defined by its breathing pattern, we would hope to be able to identify it.

The large sample size and randomised placebo-controlled design are significant methodological strengths in the current study. A further strength is the assessment of clinical outcomes at prolonged follow-up. Previous clinical trials have produced impressive results at the end of the intervention, only for a substantial proportion to relapse in follow-up.^10^ A final advantage for this study is the heterogeneity of the sample. The broad inclusion and limited exclusion criteria mean that participants experiencing a range of psychiatric comorbidities will be eligible.

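### As written, BPAT is scheduled only in the BCT sessions, so it cannot show who benefits from BCT, although it is listed as a predictor of response

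*Protocol article*

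**What the plan says.** The Breathing control training section describes two visits: "They will conduct a 60-minute initial session with the participant (one-on-one) and a 30-minute refresher session 4 weeks later". The next sentence is the only one in the article that says when BPAT is given: "The physiotherapist will administer the Brompton Breathing Pattern Assessment Tool (BPAT) in both sessions to assess for and monitor levels of breathing pattern irregularities". In that position, the two sessions meant are the BCT sessions.

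The Befriending section says that the control "involves meeting and talking with the participant in a supportive, friendly, but non-directive manner". It adds: "It will be administered by the same clinicians (physiotherapists) at intervals and duration matching the BCT sessions". It does not mention BPAT. The participant timeline (Table 3) and the trial schematic (Box 2) list BPAT for neither arm.

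Box 1 includes among the secondary outcomes: "BPAT score (at baseline) and/or Nijmegen score (at baseline), to predict response to treatment". tcCO2 before or during seizures is named in the same item. The Discussion gives the purpose: "If the intervention is only effective in a subgroup defined by its breathing pattern, we would hope to be able to identify it".

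**The concern.** Asking whether a marker identifies the people in whom BCT works is a question about effect modification: does the difference between BCT and Befriending change with the marker? Answering it needs the marker in both arms. Within BCT alone, one sees only that participants with one level of BPAT remit more often than those with another. A factor that forecasts remission equally well under Befriending gives the same picture.

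The stake is one secondary-outcome predictor and any statement that BCT suits people with a particular observed breathing pattern. This cannot be left to the analysis plan. A plan can specify an interaction term, but it cannot recover BPAT scores that were never taken in controls. Recruitment began in February 2024, so if the article is followed as written, each control who passes the first session without a BPAT is lost to this question.

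**Working it through.** **Plan's own figure.** The article gives no calculation for BPAT, so the sample size is reproduced to obtain the evaluable number. Inputs from the sample size section: 40% versus 20% remission, 80% power, two-sided 5%, 25% drop-out.

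- Per arm, pooled variance: n = [1.96·√(2·0.30·0.70) + 0.8416·√(0.40·0.60 + 0.20·0.80)]² / 0.20² = (1.270 + 0.532)² / 0.04 ≈ 81.2, so 82.
- With drop-out: 82/0.75 = 109.3, so 110 per arm and 220 in total. The stated figure reproduces.

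**Can BCT-arm data identify a predictor?** Assumptions, not in the article: half of each arm has high BPAT, and BCT remission is 50% with high and 30% with low BPAT. The BCT mean is then the planned 40%. Three sets of control rates all average 20%, as planned:

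| Control rates, high / low BPAT | BCT effect, high BPAT | BCT effect, low BPAT | Meaning |
|---|---|---|---|
| 20% / 20% | 50 − 20 = 30 points | 30 − 20 = 10 points | BPAT modifies the effect (interaction 20 points) |
| 30% / 10% | 50 − 30 = 20 points | 30 − 10 = 20 points | Prognostic only on the risk-difference scale |
| 26.6% / 13.4% | odds ratio 2.76 | odds ratio 2.76 | Prognostic only on the odds-ratio scale |

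The BCT data are the same in every row: a 20-point gap and an odds ratio of (0.5/0.5)/(0.3/0.7) = 2.33. No sample size in the BCT arm alone can tell the rows apart.

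**How often would a within-BCT test be significant?** With 82 evaluable in BCT, split 41 and 41, and a pooled null variance:

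- z = [0.20·√41 − 1.96·√(2·0.40·0.60)] / √(0.50·0.50 + 0.30·0.70) = (1.2806 − 1.3579)/0.6782 = −0.11.
- Power is Φ(−0.11), about 45%. With an unpooled standard error it is Φ(0.20/0.1059 − 1.96), about 47%.

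This rate applies whether BPAT is a true modifier or only prognostic.

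**What would the two-arm analysis deliver?** For the 20-point interaction in the first row, with 41 in each of four cells:

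- SE = √[(0.25 + 0.21 + 0.16 + 0.16)/41] = 0.138.
- Power is Φ(0.20/0.138 − 1.96) = Φ(−0.51), about 31%.

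The interaction is the right question, but this trial can answer it only weakly.

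**The case against.** The strongest objection is that one-arm collection is inferred from silence. A reader might infer that BPAT is definitely withheld from controls, and the article does not support that. The measures section and Box 1 describe BPAT with no arm limit. Another one-arm procedure is labelled as such in Table 2 ("Breathing exercises (BCT participants only) and adherence diary"), and BPAT carries no such label. Table 3 omits BPAT for both arms, so it is no evidence of a difference between them. A condensed article may also leave the content of the control session to the full protocol. All of this stands, and it limits the point to what is scheduled as written. It does not remove the point, because the only scheduling sentence belongs to BCT and would need correcting even if BPAT is in fact taken in both arms.

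A reader might also infer that a within-BCT test is planned, or that BCT will end up restricted to the wrong people. The article states no such test, and its subgroup aim is worded as a hope. BPAT is one of several candidates joined by and/or. Nijmegen is collected from everyone before randomisation and is a stratification factor. tcCO2, where monitored, comes from the standard-care work-up. Both can be tested across arms, so the wider question of a breathing-related subgroup stays open to study.

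A third tempting reading is that the unblinded physiotherapist biases the BPAT rating. If BPAT is taken in BCT only, every rated participant has the same known allocation, so no difference between arms can arise from it. That risk appears only once BPAT is taken in both arms after allocation is known, and it is a cost of the fix.

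**Conclusion.** The point holds in a limited form. As written, BPAT is scheduled only in the two BCT sessions, and nothing says that it is taken in Befriending. If that schedule is followed, the BPAT part of the predictor outcome cannot distinguish effect modification from prognosis, and no later analysis can repair this. In the example, a significant within-BCT association appears in about 45% of trials whether or not the BCT effect varies with BPAT. That figure rests on an assumed 50:50 split, assumed remission of 50% and 30%, and 82 evaluable BCT participants. The lack of identifiability does not depend on those values.

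The primary comparison, the sample size of 220 and the Nijmegen and tcCO2 predictors are unaffected. The matter should be corrected, but it does not threaten the trial's main result.

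**What to change.** State in the BCT and Befriending sections and in Table 3 that BPAT is recorded at the start of session 1 in both arms, before any session content. Define prediction for BPAT as an arm-by-BPAT interaction on Week 12 remission, with BPAT as a continuous score and the effect scale named. Report it cautiously, with a confidence interval, given power of about 31% under the assumptions above. If BPAT is already taken in both arms, only the text and table need correcting. If it is not, limit this analysis to participants of both arms randomised after the change; power would then be lower still.

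Costs: about one minute of observation per control participant by the same physiotherapist, a small risk of drawing controls' attention to their breathing, and a rating by someone who knows the arm. Rating before allocation is disclosed would remove the last of these, but it would add a separate physiotherapist assessment for every participant.

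If BPAT is not wanted in Befriending, relabel it as prognostic within BCT only, draw no subgroup-benefit conclusion from it, and test prediction with Nijmegen and tcCO2. This costs nothing in data collection.
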